#### Implementation {16c}

An experienced sub-investigator, not involved in any other aspect of this study, will use SPSS 25.0 to generate a computerized random-number list, which will allocate participants to either one of the two groups. Participants who fulfill the inclusion criteria will be recruited by the neurosurgeons involved in the PRE-EASE trial. Eligible participants will be randomly assigned to their respective interventions according to the list generated by the computerized random-number list generator.

### Assignment of interventions: blinding

#### Who will be blinded {17a}

The doctors in charge of the postoperative pain evaluation will be blinded, along with the outcome assessors and data analysts.

#### Procedure for unblinding if needed {17b}

The design is open label with only the outcome assessors and data analysts being blinded, so unblinding will not occur.

### Data collection and management

#### Plans for assessment and collection of outcomes {18a}

The primary outcome of interest will be recorded by an electronic memory system, which will include both valid and invalid presses for butorphanol demand in the 48-h postoperative period. The online recording system of the PCA demand will only be accessible to the sub-investigators blinded to the study. Secondary outcomes will be postoperative patient-reported scores, collected by a group of blinded research members in charge of the postoperative pain evaluation. At completion of the 6 months’ follow-up data collection, we will perform a data quality audit. An investigator will sample every participant file and check for missing data.

#### Plans to promote participant retention and complete follow-up {18b}

Follow-up will be conducted on day 3, at weeks 1, 2, 4, and 6, and at months 3 and 6 by an experienced research member blinded to the study. All the participants will complete a 6 months’ follow-up. Follow-up data collection will either be done in person during the patient follow-up visits or by contact via telephone. Any participants who do not complete the entire 6 months’ follow-up process due to deviation from intervention, discontinuation for personal reasons, or failure of contact will not be replaced by other patients. Participants will be allowed to withdraw their consent or discontinue participation without any restriction at any time throughout the study, and further data associated with the trial will be collected.

#### Data management {19}

The primary outcome will be recorded in an online recording system accessible only to sub-investigators blinded to the study. Secondary outcomes will be postoperative patient-reported scores, collected by a group of blinded research members in charge of the postoperative pain evaluation. At completion of the 6 months’ follow-up data collection by a blinded research member, we will perform a data quality audit. All data collected will be stored in a secure location by the lead investigator, undisclosed to other research members.

#### Confidentiality {27}

All personal information about the participants will be collected and stored in a secure cabinet by the lead investigators, throughout the duration of the study, to guarantee confidentiality. Only the lead investigator will have access to the files corresponding to the personal data of the participants.

#### Plans for collection, laboratory evaluation, and storage of biological specimens for genetic or molecular analysis in this trial/future use {33}

This trial does not involve collecting, laboratory evaluation, or storage of biological specimens for genetic or molecular analysis.

### Statistical methods

#### Statistical methods for primary and secondary outcomes {20a}

Statistical analyses will be performed using the statistical package SPSS software 25.0. A Kolmogorov-Smirnov test will be used to assess normality of variables. Data for normal distribution will be presented as mean ± SEM (standard error of the mean). Variables for skewed distributions will be described as median and interquartile range (IQR). Categorical variables will be expressed as frequencies with percentages.

Comparisons between the groups will be carried out using an independent *t* test to compare normally distributed data, the Mann-Whitney *U* test for skewed data, and a χ^2^ test or Fisher’s exact test to compare categorical data such as safety analyses with the incidence of AEs. For numerical data collected at different time points throughout the course of 6 months (e.g., PCA cumulative consumption of butorphanol, PONV, RSS, PSS, and ODI), repeated measures analysis of variance will be performed between the two groups. The significance level will be set at *P* < 0.05.

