### Outcomes {12}

Clinical and demographic characteristics such as gender, age, weight, BMI, ASA status, type of surgery (laminoplasty or laminectomy), level of spine to be treated (cervical, thoracic, lumbar, or sacral), number of levels to be treated (1, 2, 3, 4 levels or more than 4 levels), and Oswestry Disability Index (ODI) will be recorded. After the operation, the duration of surgery, length of incision (in millimeters), and volume of local anesthesia (in milliliters) injected for preeemptive infiltration will be recorded. Postoperative complications such as postoperative pain due to spinal cord or nerve injury, wound infection, wound hematoma, delirium, serious adverse effects, and death may affect the follow-up process. Other complications such as allergic reaction, local or systemic toxicity, changes in wound healing, or increased wound drainage will be closely monitored.

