### Primary outcome

The primary outcome will be the cumulative butorphanol dose during the 48 h after surgery via the PCA device.

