### Sample size {14}

Ersayli et al. reported that total morphine consumption at 24 h was 13.2 ± 4.1 mg after lumbar discectomy for patients who received local wound infiltration of bupivacaine alone just before incision [14]. The analgesic effect of 1 mg morphine is the same as that of 3.75–7 mg butorphanol. This dose of morphine could be converted into an equianalgesic dose of butorphanol (with conversion factor 1 mg morphine = 3.75–7 mg butorphanol). Therefore, we have estimated that total butorphanol consumption will be about 120.0 ± 90.0 mg at 48 h after laminoplasty or laminectomy for the patients who received preemptive analgesia with local anesthetics.

Nakai et al. suggested that local wound infiltration by addition of betamethasone could reduce the dose of analgesics by about 45% in the 24 h after lumbar discectomy [18]. Therefore, we hypothesize that the cumulative butorphanol consumption during the 48 h after lumbar discectomy will be 120.0 ± 90.0 mg in the control group and 70.0 ± 50.0 mg in the treatment group. Based on a 90% power with a two-sided α of 0.05 and a dropout rate of 20%, we have calculated that at least 116 patients (58 per group) will be required.

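### The primary comparison is left to a normality test on the trial data, although the trial is sized for a difference in means; one covariate-adjusted mean-difference analysis should be named instead

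*Protocol article*

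**What the plan says.** The primary outcome is a single total per patient: "The primary outcome will be the cumulative butorphanol dose during the 48 h after surgery via the PCA device" (Primary outcome).

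The Sample size section plans for "120.0 ± 90.0 mg in the control group and 70.0 ± 50.0 mg in the treatment group", with 90% power, two-sided α of 0.05 and 20% dropout, and concludes that "at least 116 patients (58 per group) will be required".

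The section on statistical methods for primary and secondary outcomes starts from a pretest: "A Kolmogorov-Smirnov test will be used to assess normality of variables". Normally distributed variables go to an independent t test and skewed ones to Mann-Whitney. No separate rule is given for the primary outcome, and no covariate appears. The same section lists "PCA cumulative consumption of butorphanol" among the repeated data for which repeated-measures ANOVA will be used.

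The Outcomes section records type of surgery, spine region and "number of levels to be treated (1, 2, 3, 4 levels or more than 4 levels" at baseline. The Intervention description sets the infiltrated volume at 10 ml per level. Type of surgery returns only as a subgroup factor, under the methods for additional analyses. Number of levels is not named in any analysis.

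**The concern.** The t test addresses a difference in mean dose. Mann-Whitney addresses whether doses in one arm tend to rank below those in the other. When spread differs between arms, as the plan expects (SD 90 against 50), these are different questions and can have different answers. Here the choice between them is made by a test on the outcome data, so the confirmatory hypothesis is known only after the data are in. If the rank test is chosen, the planned test gives no estimate of milligrams saved, and the power calculation no longer describes the test that is run.

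The comparison is also unadjusted in a population running from one level to more than four, across all spine regions, although the likely prognostic factors are already collected. Any precision they offer is given up.

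**Working it through.** **Inputs from the protocol article (Sample size).** Means 120 and 70 mg, SDs 90 and 50 mg, power 90%, two-sided α 0.05, dropout 20%, 58 per arm.

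**Assumptions.** The shape of the dose distribution (normal, gamma or lognormal), the variant of the Kolmogorov-Smirnov test, and the R² of the baseline factors. The document gives none of these.

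**1. Reproducing 116.**
- SD = √((90² + 50²)/2) = √5300 = 72.8 mg; difference = 50 mg.
- Normal approximation: n = 2 × (1.960 + 1.282)² × 5300 / 50² = 44.6, so 45 per arm.
- With the t distribution, 46 per arm (power 90.3% pooled, 90.1% Welch).
- 46 / 0.8 = 57.5, so 58 per arm and 116 in total.

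The stated size is exactly that of an unadjusted t test on means.

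**2. Do the planning figures suggest skew?** A normal curve would put Φ(−120/90) = 9.1% of controls and Φ(−70/50) = 8.1% of treated patients below 0 mg, which is impossible for a dose. If these SDs are right, some skew is likely.

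**3. Which test would the pretest choose?** Simulation with 40,000 trials per setting, 46 per arm, planned means and SDs, pretest in each arm, t test used only if neither arm rejects normality:

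| Shape | Mann-Whitney chosen, Lilliefors-corrected | Mann-Whitney chosen, uncorrected | Power, t test | Power, Mann-Whitney | Tests disagree at 0.05 |
|---|---|---|---|---|---|
| Normal | 10% | 0% | 90% | 88% | 5% |
| Gamma | 90% | 15% | 93% | 86% | 8% |
| Lognormal | 98% | 46% | 94% | 96% | 5% |

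Repeat simulations agree to within 1–2 percentage points for the corrected test and the powers. Under gamma data the whole pretest rule, in its corrected form, has 86% power.

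**4. Type I error.** With identical distributions in both arms, the rule rejects in about 5% of trials for all three shapes (0.047–0.052, corrected pretest).

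**5. Equal means, unequal spread.** Gamma data, both means 120 mg, SDs 90 and 50, 46 per arm: the t test rejects in 5.3% of trials, Mann-Whitney in 17.9% and the corrected pretest rule in 17%. With both means at 95 mg, midway between the planned values, the rule rejects in about 25%. These rejections are not errors for the rank hypothesis, but they show that a significant result need not mean a difference in mean dose.

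**6. Covariate adjustment.** The confidence interval scales with √(1 − R²). Unadjusted half-width at 46 per arm: 1.96 × 72.8 × √(2/46) = 29.8 mg.

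| Assumed R² | Half-width (mg) | Narrowing, 1 − √(1 − R²) |
|---|---|---|
| 0.05 | 29.0 | 3% |
| 0.10 | 28.2 | 5% |
| 0.20 | 26.6 | 11% |
| 0.30 | 24.9 | 16% |

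**The case against.** The best defence is that this is a common convention and does limited harm. Type I error holds when the distributions are identical, the two tests agree in at least 92% of trials, and Mann-Whitney is the stronger test under lognormal data. All of that stands. It limits the size of the problem but does not settle which hypothesis is being tested.

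A reader might go further on several points, and the document does not support it:

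- **That the doses cannot be normal and Mann-Whitney is almost certain.** The 120 ± 90 mg is a planning estimate. The one observed spread quoted in the Sample size section, 13.2 ± 4.1 mg of morphine at 24 hours, would put only Φ(−13.2/4.1) = 0.06% below zero. At that coefficient of variation (0.31), the corrected test rejects normality in about 30% (gamma) or 51% (lognormal) of trials. The protocol also does not say whether the test is corrected. The direction of the choice is therefore not established, only its dependence on the data.
- **That repeated-measures ANOVA is a third test of the primary outcome.** It is reserved for data collected at several time points. The primary outcome is one total, and the four period doses are a listed secondary outcome, so they are the natural target. A clarifying phrase is enough.
- **That an unadjusted analysis is an error.** It is valid in a randomised trial and matches the sample size. The gain from adjustment depends wholly on an R² that the document does not give. Nor is type of surgery ignored, since it is a subgroup factor.
- **That reporting mean ± SEM undermines the confirmatory result.** It is a matter of presentation, and applies only to variables judged normal.

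It could also be said that such detail belongs in an analysis plan that is not shown. That defence has force for the choice of covariates. It does not cover the pretest, which the protocol article states as a rule and which an analysis plan would have to overturn.

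**Conclusion.** The point holds as a fault in what the protocol fixes, and should be corrected. The primary test, and with it the hypothesis, depends on a normality test of the trial data, while the sample size presumes a difference in means.

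Its size is moderate. If the planned means and SDs are right, the data are gamma or lognormal and the pretest is corrected, about 90–98% of trials would go to the rank test, with power of about 86% or 96% against 92–94% for the t test. The two tests would give different answers at 0.05 in about 5–8% of trials. An uncorrected pretest would choose Mann-Whitney in about 15% (gamma) or 46% (lognormal). This is not a general inflation of type I error.

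Adjustment for recorded baseline factors is an improvement, not the repair of an invalid analysis. It is worth about 3–16% in interval width over the assumed R² range, and close to nothing if those factors are not prognostic.

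**What to change.** Before unblinding:

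- Drop the normality pretest for the primary outcome.
- Name one primary analysis: a linear model for the 48-hour butorphanol dose with treatment, number of levels, type of surgery and spine region, with heteroscedasticity-consistent standard errors. Report the adjusted mean difference in mg with a 95% CI.
- Keep Mann-Whitney as a sensitivity analysis that does not decide the result.
- State that repeated-measures ANOVA, where applied to butorphanol, concerns only the secondary period doses.

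The cost is a change of wording, since every covariate is already collected. The model spends a few degrees of freedom, so rules for grouping sparse level or region categories should be written in advance. The sample size need not change.

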### Objectives {7}

We hypothesize that preemptive local infiltration of betamethasone plus ropivacaine helps relieve postoperative pain, reduces the request for postoperative analgesics, and promotes early rehabilitation without significant risks.

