## Discussion

This trial will be a PROBE study. It will have better application in routine clinical practice, along with the clinical outcomes of a large simple research, which will permit a broader patient population and will include the advantage of randomization and an extensive evaluation of endpoints by blinded experts [19]. To our knowledge, there has been no attempt in the past to infiltrate laminoplasty or laminectomy with a preemptive local administration of betamethasone and ropivacaine. This study will add significant new knowledge to the effect and feasibility of preemptive wound infiltration of betamethasone.

Due to its large particles occluding the blood vessels supplying the spinal cord, betamethasone was previously reported to result in infarction of spinal cord after epidural analgesia [20]. However, we speculate that local peri-incisional infiltration of betamethasone is safe, as betamethasone has previously been used for intralesional [21], local infiltration [22], intramuscular [23], and intra-articular injections [16]. Local infiltration of steroid hormones will undeniably present the risk of delayed wound healing or local infection. However, we intend to use the lowest possible concentration of betamethasone for local infiltration based on the previous literature [15, 16, 22, 24], and thus this concentration should be considered safe. Wound healing and infection will be closely observed. The study will be immediately terminated in case of serious adverse reactions by the PRE-EASE Trial Management Group.

There are still some limitations regarding our study. Firstly, this is a single-center study; a multicenter study would be helpful in providing more significant data. In addition to incisional pain, acute pain after laminoplasty or laminectomy may be followed by long-term chronic pain that may not only originate from the incisional wound, but may also include neuropathic pain from spinal cord damage and nerve root injury. Another possible limitation of this study is that it will only involve infiltration of the surrounding tissue of the incision site. Therefore, we would like to suggest a further detailed study, regarding whether local betamethasone injection into the affected nerve roots before closure could be beneficial for postoperative pain after laminoplasty or laminectomy.

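### The hypothesis claims no significant risks, but AE incidence is analysed only by a difference test at P < 0.05, which cannot support absence of excess risk at 58 per arm

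*Protocol article*

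**What the plan says.** All references are to the protocol article.

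- Objectives {7}: the hypothesis covers pain relief, analgesic demand and recovery, and adds that the treatment "promotes early rehabilitation without significant risks". No quantity is attached to the risk part.
- Statistical methods {20a}: categorical variables are summarised as counts and percentages. Groups are compared by a chi-square test or "Fisher’s exact test to compare categorical data such as safety analyses with the incidence of AEs". For all tests, "The significance level will be set at *P* < 0.05".
- Sample size {14}: the calculation uses butorphanol dose only, "120.0 ± 90.0 mg in the control group and 70.0 ± 50.0 mg in the treatment group", and concludes that "at least 116 patients (58 per group) will be required".
- Discussion: the authors accept that "Local infiltration of steroid hormones will undeniably present the risk of delayed wound healing or local infection".

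Safety is also addressed outside {20a}. The POSAS score at 6 months is a secondary outcome for wound healing, the Trial Steering Committee assesses whether AEs are related to the interventions, and an independent Data Monitoring Committee reviews participant safety. Serious life-threatening AEs lead to termination.

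**The concern.** The article fixes four things that do not fit together: a hypothesis that risk is not materially raised, a test designed to find a difference, a significance level, and a sample size set by another outcome. A difference test can provide evidence of harm. When it is not significant, it says only that the data did not show harm, and in a small trial that is the likely result for an uncommon harm whether or not the harm exists.

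At stake is the conclusion on delayed wound healing, wound infection and steroid-related events. The first two are risks that the Discussion itself names. With no interval or margin in the plan, nothing stated would tell a reader how large an excess the trial has ruled out.

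**Working it through.** **Step 1. Reproduce the sample size.** Inputs from {14}: means 120 and 70 mg, SDs 90 and 50 mg, two-sided alpha 0.05, power 90%, dropout 20%.

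- Pooled SD = √((90² + 50²)/2) = √5300 = 72.8; difference = 50.
- Normal approximation: n = 2 × (1.960 + 1.282)² × 5300/2500 = 44.6, so 45 per arm.
- With the t distribution: 46 per arm (power 0.903).
- 46/0.8 = 57.5, rounded up to 58 per arm, 116 in total.

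The stated figure reproduces. Harms play no part in it.

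**Step 2. Miss rates of the stated tests.** The article gives no baseline harm rate, so the rates below are assumptions. {20a} does not state sidedness; two-sided 0.05 is taken from {14}. Method: enumerate every pair of event counts (a in control, b in treatment), weight each by Bin(a; n, p0) × Bin(b; n, p1), and sum the weights where P < 0.05 with b > a. The miss rate is 1 minus that sum.

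| Control vs treatment | Fisher, 58/arm | Uncorrected chi-square, 58/arm | Fisher, 46/arm |
|---|---|---|---|
| 2% vs 6% | 95% | 83% | 98% |
| 2% vs 10% | 74% | 55% | 84% |
| 5% vs 10% | 92% | 83% | 94% |
| 5% vs 15% | 69% | 55% | 76% |
| 10% vs 20% | 76% | 67% | 82% |
| 5% vs 20% | 39% | 28% | 51% |
| 5% vs 25% | 17% | 11% | 28% |
| 10% vs 30% | 28% | 20% | 41% |

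The last column is the number left after the planned 20% dropout. The smallest rises fare worst: at 58 per arm Fisher misses 2% vs 4% in 99% of trials.

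**Step 3. What a non-significant result leaves open.**

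- With no control events, Fisher needs 6/58 treated events for P < 0.05 (P = 0.027). A result of 5/58 vs 0/58 gives P = 0.057.
- For 5/58 vs 0/58 the observed difference is 8.6 points. The Wilson limits are 3.7% to 18.6% for 5/58 and 0% to 6.2% for 0/58. Newcombe's interval is 8.6 − √((8.6 − 3.7)² + 6.2²) = 0.7 to 8.6 + (18.6 − 8.6) = 18.6 points. So a result labelled non-significant is compatible with an excess of almost 19 points.
- That P value is specific to Fisher. The uncorrected chi-square is 116 × (5 × 58)²/(58 × 58 × 5 × 111) = 5.23, P = 0.02. With 2.5 expected events per arm, Fisher would be the usual choice.
- For 0/58 events the exact two-sided 95% upper limit is 1 − 0.025^(1/58) = 6.2%.

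**The case against.** The strongest reply has four parts.

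1. *The article contains no rule that P > 0.05 means safe.* This stands. A reader might infer that rule from the risk clause in {7} together with the test in {20a}, but {20a} says only that incidences will be compared. The point is that the stated method cannot support the stated hypothesis, not that the authors have committed to misreading it.

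2. *AE tests are not the only safety assessment.* This also stands. POSAS, the steering committee's causality review, the Data Monitoring Committee and the termination rule all bear on safety. None of them gives a statistical basis for excluding an excess AE risk, and POSAS is a scar score that does not count infections or gastrointestinal events.

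3. *Several-fold rises are not always missed.* This is correct. At 58 per arm Fisher has power of 61% for 5% vs 20%, 83% for 5% vs 25% and 72% for 10% vs 30%. A reader might infer from the low-rate rows that the trial is blind to any several-fold harm; the calculation does not support that.

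4. *Low power for rare harms is normal in 116 patients, and interval methods belong in the analysis plan.* The first half is accepted, and no larger sample is asked for. The second would settle the matter if the article were merely silent. It is not: it states both the risk hypothesis and the test, and the mismatch lies between those two.

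**Conclusion.** The concern holds in limited form. The risk part of the hypothesis has no quantitative criterion, and the only statistical method stated for AE incidence is a difference test that cannot support it. For two- and three-fold rises from baselines of 2% to 5%, Fisher's test at 58 per arm misses at least 69% of the time, and it misses a five-fold rise from 2% in 74%. For commoner harms with larger rises, detection is more likely than not at 58 per arm, though only about even for 5% vs 20% at 46 per arm.

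These sizes rest on assumed event rates, because the article gives none, and on two-sided testing. The mismatch between hypothesis and test does not depend on them. This is a worthwhile, inexpensive improvement in what the trial can claim. It does not affect the primary analysis or the sample size.

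**What to change.** In {20a}: for wound infection, delayed wound healing and steroid-related AEs, report the risk in each arm and the risk difference with a 95% confidence interval (Newcombe or exact). Make that interval the basis for any safety statement, worded as the excess risk that the upper limit excludes. Keep chi-square and Fisher P values as descriptive, and state that P > 0.05 is not taken as evidence of no risk.

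In {7}: restate the safety part of the hypothesis as an aim to estimate the excess risk of wound and steroid-related AEs.

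Cost: a few sentences and some intervals from data already planned, with no extra patients or visits; the per-arm percentages are already in {20a}. The downside is a more modest safety claim. With no events in either arm of 58, the upper limit for the excess would still be about 6 percentage points.

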### Postoperative recording parameters for up to 48 h

The parameters will be recorded at 2, 4, 8, 24, and 48 h after surgery by a research member, who will visit each patient in person. Pain scores will be measured using the VAS score: an 11-point VAS score during movement (VAS_M_) and at rest (VAS_R_) will be recorded, with 0 indicating no pain and 10 indicating the most severe pain imaginable.

Time of first analgesic demand will be indicated by the first press of the analgesic demand button on the PCA device. The time of first analgesic demand, total press count, the cumulative butorphanol dose for four separate periods (0–4, 4–8, 8–24, and 24–48 h), and total butorphanol dose at 48 h will be recorded.

The Patient Satisfaction Score (PSS) used in this study will comprise points 1–4, based on the study by Mobbs et al. [17].

Postoperative nausea and vomiting (PONV) and Ramsay Sedation Scale (RSS) scores will also be recorded. PONV will be measured using an ordinal scale with the following values: 0 no nausea, 1 mild nausea not requiring treatment, 2 nausea requiring treatment, 3 vomiting. The RSS uses a 6-point scale to assess sedation levels, with 1 indicating agitated, anxious; 2 cooperative; 3 only responds to commands; 4 strong response to glabellar tapping or noisy stimulants; 5 weak response to glabellar tapping or noisy stimulants; 6 no response.

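### The Ramsay score has its desirable value inside the scale (2) but is compared as a group mean, so a real improvement can cancel out or be read backwards

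*Protocol article*

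**What the plan says.** The section on postoperative recording parameters for up to 48 h introduces the scale with "The RSS uses a 6-point scale to assess sedation levels". Its anchors are "with 1 indicating agitated, anxious; 2 cooperative; 3 only responds to commands; 4 strong response to glabellar tapping or noisy stimulants", then "5 weak response to glabellar tapping or noisy stimulants; 6 no response". The list of secondary outcomes includes RSS at 2, 4, 8, 24 and 48 h after surgery.

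Statistical methods {20a} opens the relevant sentence with "For numerical data collected at different time points throughout the course of 6 months" and continues with "e.g., PCA cumulative consumption of butorphanol, PONV, RSS, PSS, and ODI), repeated measures analysis of variance will be performed between the two groups". RSS is therefore assigned by name to an analysis of group means. The protocol sets no threshold for agitation or over-sedation and does not analyse the two ends of the scale separately. Neither state appears among the adverse-event rows of Table 1.

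**The concern.** A comparison of means can be interpreted only if a higher code is consistently better or consistently worse. RSS as anchored here does not meet that condition: one agitated patient (1) and one who responds only to commands (3) average to 2, the same as two cooperative patients.

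This differs from the familiar objection that an ordinal score is being treated as a number. The Mann-Whitney test, which the plan names for skewed data, also ranks 1 below 2 below 3, and so does an ordinal model on the raw score. The order of the codes is not the order of benefit.

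The matter is relevant in this trial because Objectives {7} expects both better pain relief and less demand for analgesics. It is a reasonable inference, though the protocol does not state it, that less pain could reduce agitation while less butorphanol could reduce sedation. Both changes move patients towards 2, from opposite sides. Two errors could follow: a real improvement that the test misses, or a significant difference read in the wrong direction.

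**Working it through.** **Inputs.** The RSS anchors are from the section on recording parameters up to 48 h. The 58 per arm and two-sided α of 0.05 are from Sample size {14}. The protocol gives no RSS frequencies, so every distribution below is an assumption, and a range is shown.

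**The plan's own figure.** There is none for RSS. The 58 per arm does reproduce from the primary outcome. The pooled SD is √((90² + 50²)/2) = 72.8 mg and the difference is 120 − 70 = 50 mg. A t test with 90% power needs 46 per arm, and 46/0.8 = 57.5, rounded up to 58.

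**Formulas, one time point.** For shares p_k at score k:
- mean = Σ k·p_k
- variance V = Σ (k − mean)²·p_k
- SE of the difference = √((V_control + V_treatment)/58)
- z = difference/SE
- power ≈ Φ(|z| − 1.96) + Φ(−|z| − 1.96)

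**Balanced shifts, 20/60/20 vs 5/90/5 (% at RSS 1/2/3).** Control mean = 0.20·1 + 0.60·2 + 0.20·3 = 2.00. Treatment mean = 0.05·1 + 0.90·2 + 0.05·3 = 2.00. The difference is 0, so power equals the 5% error rate.

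**Nearly balanced, 15/65/20 vs 5/90/5.** Means are 2.05 and 2.00, and variances 0.3475 and 0.10. SE = √(0.4475/58) = 0.0878, z = 0.05/0.0878 = 0.57, power about 9%.

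**Mainly agitation, 30/60/10 vs 5/90/5.** Means are 1.80 and 2.00, and variances 0.36 and 0.10. SE = √(0.46/58) = 0.0891, |z| = 0.20/0.0891 = 2.25, power about 61%. In the simulation every significant result had the better arm with the higher mean.

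**Range of cases.** The powers of the mean test and Mann-Whitney come from simulation. The Fisher column compares the proportion not at RSS 2; where two figures are given, they are from exact enumeration and from simulation.

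| Control (RSS 1/2/3[/4], %) | Treatment | Means | Mean test | Mann-Whitney | Fisher, not RSS 2 |
|---|---|---|---|---|---|
| 20/60/20 | 5/90/5 | 2.00 vs 2.00 | 5% | 6% | 96% |
| 20/60/20 | 10/80/10 | 2.00 vs 2.00 | 5% | 5% | 59–62% |
| 15/65/20 | 5/90/5 | 2.05 vs 2.00 | 9% | 10% | 88–89% |
| 30/60/10 | 5/90/5 | 1.80 vs 2.00 | 60–61% | 65% | 96–97% |
| 5/60/25/10 | 2/88/8/2 | 2.40 vs 2.10 | 77–78% | 78% | 92% |
| 5/60/35 | 5/85/10 | 2.30 vs 2.05 | 79–80% | 82% | 83% |
| 5/65/30 | 5/90/5 | 2.25 vs 2.00 | 85–86% | 88% | 88% |
| 0/65/35 | 0/90/10 | 2.35 vs 2.10 | 91–92% | 92% | 88% |

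**Separate tests of each end (Fisher).** For 15/65/20 vs 5/90/5, RSS 1 (15% vs 5%) has about 31–32% power and RSS of 3 or more (20% vs 5%) about 60–61%. For 20/60/20 vs 5/90/5, each end (20% vs 5%) has about 60%. These tests show direction, but each is much weaker than the combined comparison.

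**The case against.** The protocol describes RSS as a measure of sedation and lists it beside nausea and vomiting, which suits a one-directional opioid side effect. It nowhere says that 2 is best, and its hypothesis mentions neither agitation nor sedation. If agitation is rare or equal between the arms, the mean comparison does its job. In the case with no agitation at all, it is slightly more powerful than the dichotomy (91–92% against 88%). This stands, and it limits the point.

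A reader might infer that a treatment reducing both agitation and sedation will necessarily show no difference. The documents do not support that. Full cancellation needs shifts of nearly equal size, and nothing in the protocol says how common either state will be.

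The planned model also covers five visits, whereas the illustration uses one. If agitation and sedation occur at different visits, a group-by-time contrast may pick up a difference. That is correct, but the contrast would still not say whether the difference was a benefit.

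Replacing one analysis with two end-specific tests would lose power and add a second test without adjustment. This stands too, and it is why the combined proportion should be the comparison and the two ends should serve to describe direction.

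Finally, cut-offs for a secondary scale are often left to the analysis plan. Here, however, the protocol itself names the method for RSS, so the point concerns a stated choice and not an omission.

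**Conclusion.** The point holds in limited form. The protocol fixes a mean-based analysis for a scale whose anchors put the desirable state at 2, with worse states on both sides. The result can therefore miss a real improvement (about 5 to 9% power when the two shifts balance or nearly balance) or point the wrong way (when less agitation dominates). It remains usable when the change is mainly in sedation (about 77 to 86% power in the three such cases that include some agitation).

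This rests on two assumptions: that 2 is the desirable score, which follows from the anchors, and the illustrative distributions at a single time point. Severity is minor to moderate. RSS is one of many secondary outcomes, and the primary outcome, the sample size and any conclusion on butorphanol are untouched.

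**What to change.** In Statistical methods {20a}, remove RSS from the repeated-measures list and state instead:

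- Compare between arms, per patient over 0–48 h, the proportion ever recorded away from RSS 2, using the χ² or Fisher test already named in that section.
- Report any RSS 1 and any RSS of 3 or more separately, to show the direction of a difference.
- Tabulate the full score distribution by arm at 2, 4, 8, 24 and 48 h.

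The power figures above apply to the new comparison only if the assumed shares are read as per-patient shares over 48 h; the real shares may differ.

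The cost is a change of wording, with the same data, visits and software. Collapsing the scale discards the grading among sedation levels, which the table keeps. If the change turns out to be in sedation alone, the dichotomy may give up a little power against the mean test.
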